**Methods:**

10 primary care practices will be recruited to the study (5 intervention, 5 control). Within each practice, individuals at high risk of impaired glucose regulation will be identified using an automated version of the Leicester Risk Assessment tool. Individuals scoring within the 90^th^ percentile in each practice will be invited to take part in the study. Practices will be assigned to either the control group (advice leaflet) or the intervention group, in which participants will be invited to attend a 3 hour structured educational programme designed to promote physical activity and a healthy lifestyle. Participants in the intervention practices will also be invited to attend annual group-based maintenance workshops and will receive telephone contact halfway between annual sessions. The study will run from 2010–2014.

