## Methods

### Study design

This study is a clustered randomised controlled trial. Randomization will be conducted at the level of the GP practice by a trained individual who is independent of the study team. Practices were randomised (1:1) to receive control conditions or a structured education programme. A blocked design stratified for practice size was used. The study is designed to adhere to internationally recognized criteria for developing complex interventions [15] and for undertaking and reporting cluster randomised controlled trials [16]. Follow-up will be conducted at 12, 24 and 36 months in order to establish the longer-term effectiveness of the programme and determine the natural history of progression to type 2 diabetes over three years in a high risk UK cohort identified through a risk score in primary care. See Figure 1 for a flow-diagram of the study design. 

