### Sample size

This study was powered to detect a difference in change in ambulatory activity of 2000 steps per day between groups; a difference of this magnitude reflects the primary behaviour change aim of the intervention programme and is consistent with the national physical activity recommendations and the intervention effect observed in the proof of concept study that preceded this trial [9,17]. Previous studies with a follow-up of between 3 to 12 months have reported a standard deviation of change in ambulatory activity of 2500–4000 steps per day in relevant populations [9,18-20]. Therefore, in order to detect a difference of 2000 steps per day between groups, assuming a standard deviation of 4000 steps per day, a power of 90%, a significance of 0.05, a cluster size of 90 (see section titled Participants below) and an intracluster correlation coefficient of 0.02 [21], we require a minimum of 8 clusters. In order to account for potential dropout at the practice level and comply with guidance from the Medical Research Council for minimum cluster numbers [22], 10 GP practice clusters will be recruited to this trial.

This sample size will also have sufficient power to enable clinically significant differences to be detected between groups for change in important secondary outcomes. For example, based on a power of 80%, a significance of 0.05 and a intracluster correlation coefficient of 0.02 [23], the above sample size will allow for a reduction in 2-h glucose of 0.8 mmol/l (based on a standard deviation of 2 mmol/l standard deviation [24]) and a reduction in HbA1c of 0.2% (based on a standard deviation a standard deviation of 0.5% [24,25]) to be detected.

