Based on a typical GP practice of 4500 adults without known type 2 diabetes, 450 will be eligible for inclusion into the study based on the risk score. Of these we anticipated that 330 (75%) will meet the initial inclusion criteria and be invited to take part in the study. Around 100 (30%) are then expected to consent to take part, of which 10 (10%) will have screen detected type 2 diabetes and therefore excluded at baseline; therefore we anticipate the average cluster size to be 90 individuals (see sample size calculation).

Those diagnosed with diabetes over the course of the study will be informed of their diagnosis and referred back to their health care team for standard care. Progression to type 2 diabetes will be included as a secondary outcome.

Figure 1 shows the flow of the participants through the study.

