### Data analysis

The study will be reported according to the internationally recognised CONSORT statement for the reporting of cluster randomised control trials [16]. Those withdrawn from the study due to a diagnosis of type 2 diabetes will have their last observation carried forward. Sensitivity analysis, using multiple imputation, will be used to assess the effect of those missing to follow-up. Random effects regression models, controlled for baseline value and taking into account cluster, will be used to look at the difference between groups in change from baseline in continuous outcome measures after checking for normality and applying transformation techniques where necessary. Extreme outliers (more than 4 standard deviations from the mean) will be removed from the analysis. Survival curves will be calculated to estimate the cumulative incidence of diabetes. The difference in incidence of diabetes in the groups will be tested using the two-sided log-rank test. Statistical significance will be assessed at the 5% level and all analysis will be 2-sided.

Interim analysis will be conducted and reported at 12 months.

In concordance with other physical activity randomised controlled trials undertaken by our group and others [46,47], we will undertake pooled analysis of the study cohort to determine, through regression analysis techniques, the extent to which change in physical activity is associated with change in key biochemical and anthropometric variables; this will help provide additional information quantifying the strength of the association between physical activity and metabolic health in a population with a high risk of type 2 diabetes; any such analysis will be reported with the caveats inherent in undertaking additional pooled cohort analysis within the context of a randomised controlled trial.

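### The planned log-rank test for progression to type 2 diabetes ignores randomisation by practice, so its type I error exceeds 5% whenever incidence varies between practices

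*Protocol article*

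**What the plan says.** The Study design section makes the practice the unit of allocation: "Randomization will be conducted at the level of the GP practice by a trained individual who is independent of the study team". Allocation is 1:1, blocked and stratified for practice size. The abstract gives 10 practices, 5 per arm, and the Participants section says "we anticipate the average cluster size to be 90 individuals".

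The Sample size section allows for clustering. For steps it uses "an intracluster correlation coefficient of 0.02 [21], we require a minimum of 8 clusters". It applies an ICC of 0.02 again, with a different citation, to 2-h glucose and HbA1c.

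The Data analysis section handles outcomes in two ways. Continuous outcomes get random effects regression, adjusted for baseline and allowing for cluster. Diabetes incidence gets survival curves and a named test: "The difference in incidence of diabetes in the groups will be tested using the two-sided log-rank test". Significance is judged two-sided at 5%. No stratified, clustered, frailty, robust-variance or practice-level form of the log-rank test is mentioned.

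**The concern.** The variance of the ordinary log-rank statistic assumes that participants' outcomes are independent within and between arms. Under allocation by practice, differences between practices in underlying incidence also enter the comparison of arms, and that variance leaves them out. The statistic is then too variable under the null, and chance differences between two sets of five practices can be declared a prevention effect.

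The document itself gives reasons to expect incidence to vary by practice. Eligibility is the top tenth of the risk score within each practice, not an absolute cut-off. Ethnicity enters the score as a practice proportion. Diabetes is identified from fasting or 2-h glucose, and 2-h glucose is one of the measures for which the plan assumes an ICC of 0.02. Stratification is on practice size alone, and five practices per arm will not reliably balance the rest.

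At stake is a between-arm claim about diabetes prevention. Progression to diabetes is a stated secondary objective, and the Discussion says the trial should help commissioners and policy makers decide on prevention programmes.

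**Working it through.** **Inputs from the protocol article.** Practices: 10, 5 per arm (abstract). Average cluster size m = 90 (Participants). ICC 0.02 for steps, 2-h glucose and HbA1c (Sample size). Primary target: 2000 steps, SD 4000, 90% power, 5% significance (Sample size). Diabetes test: two-sided log-rank at 5% (Data analysis). No ICC for diabetes incidence is given.

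**The plan's own figure first.**
- Individually randomised size per arm: 2 × (4000 × (1.960 + 1.282) / 2000)² ≈ 84.1, rounded up to 85.
- Design effect: DE = 1 + (m − 1) × ICC = 1 + 89 × 0.02 = 2.78.
- Clusters per arm with one added for small numbers: 1 + 84.06 × 2.78 / 90 = 3.60, rounded up to 4, so 8 in total.
- A t-test on cluster means has power 74.1% with 3 clusters per arm and 91.5% with 4.

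The stated minimum of 8 therefore reproduces, and the design stage does allow for clustering.

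**Error rate of a test that omits the design effect.** If the true variance of the statistic is DE times the assumed variance, a nominal two-sided 5% test rejects a true null with probability 2 × (1 − Φ(1.96 / √DE)). At ICC 0.02: 1.96 / √2.78 = 1.96 / 1.667 = 1.176, which gives 24.0%.

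| ICC for incidence (assumed) | DE, m = 90 | True error, m = 90 | DE, m = 72 | True error, m = 72 |
|---|---|---|---|---|
| 0.001 | 1.089 | 6.0% | 1.071 | 5.8% |
| 0.005 | 1.445 | 10.3% | 1.355 | 9.2% |
| 0.01 | 1.89 | 15.4% | 1.71 | 13.4% |
| 0.02 | 2.78 | 24.0% | 2.42 | 20.8% |

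The columns for 72 per practice illustrate an assumed 20% loss (0.8 × 90 = 72).

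**Simulation check.** Ordinary log-rank test under the null; 5 v 5 practices of 90; beta-distributed practice risks; detection at annual visits; 20,000 trials per scenario. The 3-year risks of 5% to 20% are assumptions.
- ICC 0.02, no loss: 23.7% to 24.4%, matching the formula.
- ICC 0.02, assumed 7% loss per year: 21% to 22%.
- ICC 0, same loss: 5.0% to 5.3%, so the test holds its level when practices do not differ.
- t-test on practice event rates with 8 degrees of freedom, ICC 0.02: 4.4% to 4.9%.

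**A more cautious ICC.** Suppose 0.02 describes the underlying glucose measure and diabetes is a threshold on it. The ICC of the yes/no outcome is then approximately 0.02 × φ(q)² / (p(1 − p)), where p is the incidence and q the matching normal quantile.
- p = 5%: 0.02 × 0.0106 / 0.0475 ≈ 0.0045.
- p = 20%: 0.02 × 0.0784 / 0.16 ≈ 0.0098.

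Across these assumed incidences the error is about 10% to 15%.

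**The case against.** The strongest objection is to the size. The 0.02 is given for continuous outcomes, and carrying it over to diabetes incidence is an assumption. At an assumed 3-year incidence of 10%, ICC 0.02 implies a between-practice SD of √(0.02 × 0.10 × 0.90) = 4.2 percentage points, heterogeneity that the document does not support. At ICC 0.001 the error is only about 6%. This stands: 24% is a conditional figure. A reader might infer that the error is known to be far above 5%; the document fixes the direction for any positive ICC, not the amount.

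Second, the article says the study is designed to follow recognised criteria for conducting and reporting cluster randomised trials, so the short sentence might stand for a cluster-adjusted log-rank test. That is possible, but a general commitment does not change a named test, and the same paragraph mentions cluster where it means to use it. Nor is this a detail left to an analysis plan, because the test is specified here.

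Third, the endpoint is one secondary outcome with no power statement. The primary outcome and the continuous secondary outcomes, including fasting glucose, 2-h glucose and HbA1c, are analysed with cluster allowed for. This stands and limits the reach of the point.

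Two further inferences are tempting. One is that a planned confidence interval will be too narrow; the Data analysis section plans none for this comparison, only survival curves and a test. The other is that detection at annual visits, with heavily tied event times, is a second fault. The log-rank test accommodates ties, and with annual detection it kept its level in the simulation when practices did not differ.

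**Conclusion.** The point holds. The plan names an independence-based test for a comparison between randomised practices, and as written that test does not have the stated 5% level if incidence is positively correlated within practices. With 90 per practice the error is about 24% if the ICC for incidence equals the 0.02 used elsewhere in the protocol, 15% at 0.01, 10% at 0.005 and 6% at 0.001. At 0.02 it falls to about 21% with 72 per practice.

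These figures rest on an assumed ICC, equal cluster sizes and the normal approximation; the assumed 3-year risk made little difference in simulation. The conclusion is confined to the between-arm test of diabetes incidence and does not touch the primary outcome.

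**What to change.** In the Data analysis section, replace the ordinary log-rank test with one that accounts for practice and uses a small-sample reference suited to 10 clusters. The simplest choice is a two-sided t-test on practice-specific incidence rates (cases divided by person-years in each practice), with 10 − 2 = 8 degrees of freedom. Acceptable alternatives are a clustered log-rank test, a shared-frailty Cox model, or a discrete-time model over the three annual intervals with a practice effect, each with a small-sample correction. Name one before the data are analysed. Keep the survival curves by arm as description.

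The cost is a revised sentence, a little more programming and a less favourable p-value for diabetes incidence. Recruitment, data collection and conduct do not change.

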### Current status

This study gained full ethical and governance approvals from the Nottingham Research Ethics Committee 2 and the Leicestershire, Northamptonshire and Rutland Comprehensive Local Research network in April 2009. Recruitment of patients was initiated in 2010.

## Discussion

To our knowledge this will be the first study in the United Kingdom to establish the long-term effectiveness of an intervention programme designed to promote lifestyle change in those with a high risk of type 2 diabetes identified using a risk score within primary care. Whilst both the effectiveness and cost-effectiveness of lifestyle intervention programmes at preventing type 2 diabetes have been established [6,48], there has been a lack of translational research aimed at developing and evaluating a diabetes prevention programmes specifically designed for a routine health care setting in the UK. This has limited the ability of health care commissioners and policy makers to make informed evidence-based decisions regarding the implementation of regional and national diabetes prevention programmmes. This study will help address this limitation.
